|                                               |                                                                                                                                                                    |
|-----------------------------------------------|--------------------------------------------------------------------------------------------------------------------------------------------------------------------|
| Title:                                        | Rapid Diagnostic Testing and Artemisinin - Based Combination Therapy for Uncomplicated Malaria by Community Health Workers                                  |
| Short Acronym:                                | RapAct                                                                                                                                                             |
| Long Acronym:                                 | RDT and ACT for malaria by CHWs                                                                                                                                    |
| Updated on:                                   | 28 February 2006 (Final +1)                                                                                                                                        |
| Design:                                       | Multicentre comparative crossover validation study                                                                                                                 |
| Study sites:                                  | Villages in Kibaha District                                                                                                                                        |
| Study Director:                               | [name], KI                                                                                                                                                |
| Principal Investigators:                      | [name], KI
[name], MUCHS                                                                                                                             |
| Co-Investigator(s):                           | [name], MUCHS (RDT Study)
[name], MUCHS (RDT study)
[name], MUCHS (Coartem Study)                                                    |

## Study Proposal:

### RapAct

## **Rapid Diagnostic Testing and Artemisinin – Based Combination Therapy for Uncomplicated Malaria by Community Health Workers**

### **1. Background and Relevance**

#### **1.1 Malaria Treatment and ACT**

In the Roll Back Malaria (RBM) strategy and the Abuja Malaria Summit one of the six main targets is that 60 % of those suffering from malaria should have access to and be able to use correct, affordable and appropriate treatment within 24 hours of the onset of symptoms (The Africa Malaria Report, 2003).

Due to resistance of *Plasmodium falciparum* malaria to common antimalarial drugs and its health implications, most African countries are switching to artemisinin-based combination therapy (ACT) as first line treatment policy (Björkman & Bhattarai, 2005). Currently, the resistance to the first-line drug in Tanzania since 2001, sulfadoxine-pyrimethamine (SP), is developing rapidly, with high resistance pockets reaching a rate of 15 % in many areas of the country, and up to 34% in Muheza area (Hastings et al., 2002).

In Zanzibar, ACT has been implemented since 2004, and the mainland of Tanzania has decided to switch from SP to ACT in 2006. Zanzibar is using artesunate+amodiaquine as the first line treatment and Coartem®, a fixed dose combination of artemether-lumefantrine, as second line option. On the mainland Coartem will be first line treatment with quinine monotherapy as second line.

The necessity to introduce more expensive ACTs is making diagnostics of true malaria infection more important than before. The concept of home-based management, where fever alone is the indication to treat, is therefore challenged due to its built-in risk of over-treatment (O'Dempsey et al., 1993; Mkandala et al., 2000; Nsimba et al., 2003). Over-treatment increases costs and the risk of development of resistance towards the new drugs. On the other hand, a delay in diagnosis and treatment due to a lower accessibility to the correct drugs would greatly harm the possibility of fulfilling the Abuja target stated above. Evidence on the

use of ACT in community management is lacking but highly needed. For example, experience from Uganda is based on the use of chloroquine (Kallander et al., 2004).

The cost of ACT ranges from 0.9 USD for treating a child to 2.4 USD for treating an adult (Piola et al., 2005). This is making ACT 10-20 times more expensive than the current regime in Tanzania, which is SP. The price of rapid diagnostic test (RDT) (0.5-1 USD) is motivated if the diagnostic accuracy reduces the use of ACT without affecting health outcome. The cost effectiveness of RDT will depend on the prevalence of disease in a specific area.

## 1.2 Malaria diagnosis and RDT

Malaria is the leading cause of morbidity in Tanzania, accounting up to 30% of outpatient attendances and admissions at health facilities. In most of the peripheral health facilities, equipment and trained personnel to perform laboratory diagnosis of malaria are not available, and diagnosis is based on clinical criteria, mainly presence or history of fever. Unfortunately, clinical criteria for a clinical episode of malaria are quite non-specific, although “erratic fever” has been shown to be highly predictive/specific for malaria associated fever (Rooth & Björkman, 1992). The Swahili wording for this is “homa ya vipindi”. To our knowledge, the value of integrating this term in clinical algorithms has not yet been tested in alternative studies.

The RDT provides a new, simple and accurate way of determining malaria infection. Such a test in the form of dipsticks or plates are based on detection of parasite antigen in blood, and do not require the skills of a microscopist nor investments like microscope and electricity.

Evaluations of RDTs have been carried out in different settings and have shown that there is wide variability within and between products, which calls for improvement. However, most of the tests were found to be sensitive and specific, with rates of 94-100% and 89-97% respectively (Singh, Saxena & Sharma, 2002; Singh & Saxena, 2005), taking a short time to produce results (5-15 minutes), and can be performed by personnel with minimal training (Arora et al., 2003, Bell et al., 2001, Aslan et al., 2001). They indicate presence or absence of parasites, and whether the infecting species is *Plasmodium falciparum* or non-falciparum. The ability to detect low levels of parasitemia may, however, be considered a disadvantage in endemic areas, where many people carry parasites without being sick. Patients with fever and low density parasitemia may thus be mistaken as malaria patients.

Another issue is that some RDT tests, especially those based on detection of Histidine-rich protein 2 (HRP2), remain persistently positive up to three weeks after clearance of parasitemia, which has been attributed to persistence of antigens and presence of gametocytes (Arora et al., 2003; Singh & Shukla, 2002; Tjitra et al., 2001). Such tests should not be used to monitor treatment outcome.

The tests are relatively expensive, at 0.5-1 USD per test (WHO, 2000; Moody, 2002). For this reason, they were not considered cost effective for widespread use during the era of chloroquine and SP (Wongsrichanalai, 2001). However, they may well be worthwhile when treatment policies change to the more expensive ACT.

### **1.3 Community based diagnosis and treatment**

With the new approach advocated by WHO/RBM to control morbidity and mortality, i.e. making antimalarial treatment available as close to the home as possible, more people without clinical training and hence without the ability to differentiate malaria from other fevers will be involved in providing treatment. This calls for the use of simple and objective criteria in making a diagnosis of malaria.

The most likely persons to be used in Tanzania in extending the availability of antimalarials to the households are Community Health Workers (CHWs). These are community members, usually two in each village (male and female) who have been identified by village health committees to deal with health issues in their communities. They are involved in mobilizing communities and assist health workers in health facilities during Mother and Child Health care (MCH) clinics, vaccinations, and follow up of patients in their communities. In some cases, education seminars are organized for CHW on different health aspects. CHWs are not employed and hence not paid a salary. However, they are supposed to be given a token by their villages.

### **1.4 Local background**

The study will be carried out in Kibaha district, one among five districts of the Coast Region. The district is situated 40-80km west of Dar es Salaam. It is a mainly rural area with about 130,000 inhabitants (12% under the age of five) (National Census of 2002). Kibaha has two administrative councils, and 21 public health facilities (one hospital, one health centre and 19

dispensaries). There are three additional military dispensaries, three dispensaries connected to schools and a public cooperation, as well as three private dispensaries.

The district is in the equatorial rain forest geographical and climatic region, with heavy rainfalls (from 1000-2000 mm per annum) and temperatures from 24°C to 30°C. Abundant fresh water, collecting the year round, in creeks, swamps, pools and rice fields ensure the breeding of large numbers of *Anopheles gambiae* and *funestus* mosquitoes, which are the main vectors of malaria. Malaria transmission in the district occurs throughout the year (holoendemic pattern of malaria transmission), with some accentuation during the rainy season (May-July) and to a lesser extent December - January.

Among the strategies for controlling malaria adapted in the Coast Region is treatment of malaria patients with effective antimalarial drugs and the use of insecticide treated nets (ITN). The bed net voucher system is in place, where pregnant women can buy ITNs at subsidized rates to protect themselves and their children.

The MUCHS/KI Malaria group has been involved in malaria research in both Bagamoyo and Kibaha, two of the districts in the Coast region. The research group has completed an intervention to improve malaria diagnosis at health facilities. Kibaha was chosen for this phase of malaria management at community level for several reasons. This district has a well developed structure of CHWs that have been trained in community integrated management of childhood disease (c-IMCI), although they have not previously been involved in curative care. It also has a well planned organisation to support CHW from each dispensary and from a special unit at the district level. Kibaha district can be considered as a model for involvement of community health workers in preventive health care and monitoring of good health practices in their villages.

### 1.5 General rationale

- a) There is increasing evidence that correct diagnosis and prompt and appropriate treatment with effective drugs is a highly cost-effective malaria control strategy. Trained CHWs have been suggested as a tentative delivery channel for provision of antimalarial drugs in order to improve prompt treatment.
- b) Previous studies on community based management of malaria have used chloroquine but none have explored the possibility of providing ACT therapy through CHWs.

- c) RDTs provide a simple and accurate way of determining malaria infection. Studies have found different RDTs to be sensitive and specific (Singh, Saxena & Sharma, 2002; Singh & Saxena, 2005), taking a shorter time to produce results (5-15 minutes) than microscopy, and they can be performed by personnel with minimal training (Arora et al., 2003; Bell et al., 2001; Aslan et al., 2001). We will evaluate the feasibility of using trained CHWs aided by RDT to provide Coartem for malaria cases in the community.

This study represents an expressed priority by the Ministry of Health (MOH) in Tanzania and will provide results within a relatively short time-span, preceding the change of antimalarial policy in Tanzania and hence likely to have an important effect in this transformation.

Our design is addressing a controversial matter, as stated by the Board on Global Health (BGH) in Saving Lives, Buying Time: Economics of Malaria Drugs in an Age of Resistance (2004).

*“However, in high prevalence areas of sub-Saharan Africa, universal treatment of clinically suspected cases with ACTs is the safest near-term strategy, given the desperate need for rapid, in- or near-home treatment in order to save lives. Eventually, combining RDTs and ACTs in areas of Africa of low and medium malaria prevalence could reduce the number of illnesses misdiagnosed as malaria and yield major savings in terms of drug cost and delayed onset of drug resistance. In the meantime, following the introduction of ACTs in Africa, pilot programs and operational research combining ACTs and RDTs in a variety of epidemiologic settings and at-risk populations should be encouraged.”*

## 2. Hypotheses

**Hypothesis 1:** RDT used by CHWs for the identification of non-severe clinical malaria will reduce use of Coartem by 30 % without affecting health outcome.

**Hypothesis 2:** The effectiveness/parasitological cure of Coartem for the treatment of uncomplicated malaria at community level is above 90 % as assessed in a 42 day follow up in children <5 years old.

**Hypothesis 3:** The use of RDT and Coartem is well perceived by the community and will enhance health seeking behaviour.

### 3. Objectives

**3.1 General aim:** To explore malaria case management with Coartem with or without RDTs by trained CHWs at community level.

### 3.2 Study objective

To test the efficiency and effectiveness of using RDT's and the effectiveness of Coartem by CHWs for management of uncomplicated malaria at community level and to study the attitudes of these procedures by the community.

### 3.3 Specific objectives

1. To determine the proportion of children and adults who receive malaria treatment (ACT) from CHWs within 24 hours of onset of symptoms vs. later.
2. To determine the ability of CHWs to correctly assess the presence or absence of malaria using RDT's.
3. To explore reasons for potentially treating RDT negative patients with Coartem.
4. To assess the predictive value of erratic fever ("homa ya vipindi") as a clinical tool to differentiate malaria from other causes for fever.
5. To assess health status of patients in all age groups days **3 and 7** (active follow up) and up to day 28 (passive follow up) after contact with CHW.
6. To assess management cost of clinical episodes of fever by CHWs with or without RDT's.
7. To study PCR adjusted antimalarial effectiveness of Coartem treatment in children <5 years with uncomplicated malaria by trained CHWs (with or without the diagnostic support of RDT) up to day 42.

8. To explore compliance to Coartem regimen **in all age groups.**
9. To explore the attitudes of CHWs and patients towards RDT's and Coartem at community level.

## **4. Methods**

### **4.1 General study design:**

A community based intervention study with a cross-over design in which Community Health Workers (CHWs) will be trained to distribute Coartem for the management of malaria, with or without the aid of RDT.

### **4.2 Study area and sample size:**

7 villages in Kibaha district with a total population of 8000 people will be included in the study. The whole population represents the study population. A total of 22 CHWs from these villages will be involved in the study. The number of CHWs per village varies between 2 and 4 depending on the total population in the respective village. The geographic distribution of the population has been taken into consideration when determining the number of CHWs for each village. Each CHW will be responsible for between 250 and 400 people in their village. There are 5 dispensaries in the area and clinical officers from these facilities will also be involved. (See further under 4.4 & 4.6)

### **4.3 Sample unit:**

Any patient presenting with fever or a history of fever to the CHW for purpose of treatment.

### **4.4 Specific design:**

This is a cross over design in the sense that the same CHW will do malaria diagnosis alternating every week between using RDT and no RDT (clinical diagnosis only) for the entire duration of the study. The study will be performed for 16 weeks without break, preferably covering both high and low transmission seasons.

The Principal Investigator (PI) will ensure that appropriate training relevant to the study is given to CHWs to be able to collect the specimens for further investigation and be well familiarised with the procedure and interpretation of the results of the RDTs. Manufacturer's

instructions and a special training by the study supervisor prior to study initiation will assist the CHW to perform the RDT.

Training at community level will include training of CHW in:

- a) Diagnosis of malaria clinically  $\pm$  RDT
- b) Treatment with Coartem, and instructions to patients or parents of its correct intake.
- c) Collection of blood samples on filter papers and for blood-smears
- d) Information to patients when to come back for follow up
- e) Clinical and blood test follow-up, monitoring of compliance and reporting clinical data (including adverse events).

#### **4.5 Inclusion criteria:**

- a) Fever (“homa”) in the last 24 hours according to community-based guidelines prepared by the research team, based on the Integrated management of Childhood Illness (IMCI) algorithm (“simplified IMCI”).
- b) Informed consent.

#### **4.6 Exclusion criteria:**

- a) Severe clinical manifestations (according to IMCI algorithm), which require immediate referral to the closest dispensary or the Mlandizi Health Centre.
- b) Known or suspected pregnancy - pregnant women will be referred to the dispensary where they will be treated with SP.
- c) Previous enrolment within the last 28 days.

#### **4.7 Diagnosis and treatment**

Diagnosis and treatment of malaria will be based on clinical assessment + RDT for one week, and on clinical assessment only for the next week, alternating for the entire duration of the study.

The CHWs will have access to Coartem and paracetamol (but not antibiotics). Treatment will be given free of charge to patients enrolled in the study. Coartem is a fixed dose combination of artemether-lumefantrine, which is given in six doses over three days. When a diagnosis of malaria is made, the first dose of the drug will be administered by the CHW (supervised), and the remainder of the drugs in the blister pack will be given to the patient/guardian with

instructions on when and how to take them (unsupervised intake). The patients will be instructed to give locally available fatty foods with the drug, such as coconut-milk, nuts or a teaspoon of cooking oil, but no food will be distributed by the research team.

Coartem treatment is given in standard doses according to body weight as indicated in the table below. *An alternative method (in accordance with Novartis program) is to choose the correct dose based on the pictures on the Coartem dose chart.*

| Weight (kg) | Number of tablets per dose given at 0, 8, 24, 36, 48 and 60 hours | Daily dose of artemether (A) and lumefantrine (L) |
|-------------|-------------------------------------------------------------------|---------------------------------------------------|
| 5-14        | 1                                                                 | 40 mg A + 240 mg L                                |
| 15-24       | 2                                                                 | 80 mg A + 480 mg L                                |
| 25-34       | 3                                                                 | 120 mg A + 720 mg L                               |
| >35         | 4                                                                 | 160 mg A + 960 mg L                               |

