#### 4.8 Analysis:

The patients will be divided into 3 age groups for age dependent analyses: 0-4 years, 5-14 years and above 14 years.

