#### 4.11 Study products

Paracheck Pf manufactured by Orchid Biomedical Systems, India, will be used as RDT. This test has been chosen for the study because it is the one that has been identified by the MOH as the diagnostic test to be used in directing treatment with Coartem in areas where microscopy is not available. This test has been evaluated in other areas and found to be highly sensitive and specific, with rates of  $>95\%$  and  $100\%$ , respectively (Dev, 2004; Huong et al., 2002). The tests have been purchased from Biocare, Dar es Salaam. CHWs will be trained on how to perform the tests according to manufacturer's instructions.

Coartem® (Novartis, Switzerland) will be used for treatment. Coartem was purchased from the retailer (Heko Pharmaceuticals, Dar es Salaam) and repacked from packages of 2 x 8 tablets. Blisters were cut and repacked into specially developed and colour-coded packages for each patient group as determined by patient weight. The drug will be given in 6 doses as described by the manufacturer. CHWs will similarly be trained on how to administer the dose

according to manufacturer's instructions. Only the first dose will be given under supervision (of CHW) (see also 4.7).

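### Eligibility sets no age or weight floor, but the Coartem dose table starts at 5 kg, so an enrolled infant below 5 kg who is diagnosed with malaria has no dose stated in the protocol

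*Protocol*

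**What the plan says.** **Dosing (4.7).** "Coartem treatment is given in standard doses according to body weight as indicated in the table below". The table has four rows: 5-14 kg, 15-24 kg, 25-34 kg and >35 kg, with 1, 2, 3 and 4 tablets per dose. The same section allows an alternative, which "is to choose the correct dose based on the pictures on the Coartem dose chart". That chart is not reproduced in the protocol.

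**Packs (4.11).** The drug is repacked into "colour-coded packages for each patient group as determined by patient weight".

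**Eligibility (4.5, 4.6).** Inclusion needs informed consent and "Fever (“homa”) in the last 24 hours according to community-based guidelines prepared by the research team". The exclusions are severe manifestations, known or suspected pregnancy, and "Previous enrolment within the last 28 days". Neither list mentions age or weight.

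**Scope (4.2, 4.8).** "The whole population represents the study population". The age groups for analysis are "0-4 years, 5-14 years and above 14 years", so infants are included from birth.

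**Enrolment (4.13).** Everyone who meets the criteria is enrolled, and those judged to need malaria treatment receive Coartem.

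**The concern.** The eligibility rule and the dosing rule cover different sets of patients. Eligibility has no lower limit, whereas the dose table starts at 5 kg. A community health worker (CHW) who follows the protocol as written can enrol an infant under 5 kg, reach a diagnosis of malaria, and then find no row for that child.

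The stake is patient safety. Section 1.4 says these CHWs have not previously been involved in curative care, and section 6.3 gives them one week of training. For pregnant women, section 4.6 names the group and says where to send them. Infants below the table get no such instruction, so the missing row cannot safely be read as an implied exclusion. Eligibility and dosing belong in the protocol itself and would not be left to a statistical analysis plan.

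**Working it through.** **1. The table's own arithmetic.** With two doses a day, the daily amount divided by (2 x tablets per dose) should be the same in every row.

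- Artemether: 40/2 = 80/4 = 120/6 = 160/8 = 20 mg per tablet.
- Lumefantrine: 240/2 = 480/4 = 720/6 = 960/8 = 120 mg per tablet.

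The dose column is internally consistent. The problem lies only in which weights the rows cover.

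**2. Coverage of the rows.**

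- Whole kilograms from 1 to 80 that match no row: 1, 2, 3, 4 and 35.
- Read literally to one decimal, 14.1-14.9, 24.1-24.9 and 34.1-34.9 kg are also uncovered.
- If the rows mean completed kilograms, those decimal gaps close. Weights below 5 kg and exactly 35.0 kg stay uncovered.

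**3. Eligibility set against the table.** No criterion in 4.5 or 4.6 removes a patient on age or weight, 4.2 takes in the whole population, and 4.8 starts at 0 years. The weights below the table are therefore eligible, apart from infants excluded for severe illness.

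**4. Size, as a range under stated assumptions.** The protocol gives no weight distribution. The inputs are:

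- Under-fives: 12% of the district (1.4) gives 8,000 x 0.12 = 960. The 200 per 1,000 used in 4.10 gives 8,000 x 0.20 = 1,600.
- Fever rate among under-fives (4.10): 100/200 = 0.5 per child-month in the wet season and 60/200 = 0.3 in the dry season, mean 0.4.
- Period: 16 weeks, treated as 4 months. Attendance at the CHW: 80% (4.10).
- Assumption not in the documents: under 5 kg corresponds to the first 1 to 3 of the 60 months under age five, with children spread evenly by age.

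These rates reproduce the plan's own figures in 4.10. 1,600 x 0.4 x 4 = 2,560 fevers, or 1,280 per study group, and 80% of that is 1,024, as printed.

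Presentations below the table = under-fives x months/60 x 0.4 x 4 x 0.8.

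Only those judged to have malaria need a dose. Two fractions can be taken from 4.10:

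- The malaria-to-fever ratio for under-fives, 480/1,280 = 0.375.
- The planned treatment fraction for under-fives, 70% with RDT and 90% without, mean 0.80.

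| Under-fives | Months below 5 kg (assumed) | Febrile presentations | x 0.375 | x 0.80 |
|---|---|---|---|---|
| 960 | 1 | 20.5 | 7.7 | 16.4 |
| 960 | 3 | 61.4 | 23.0 | 49.2 |
| 1,600 | 1 | 34.1 | 12.8 | 27.3 |
| 1,600 | 3 | 102.4 | 38.4 | 81.9 |

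This gives about 20-100 presentations, of which about 8-80 would need a dose. Against the 2 x 2,144 = 4,288 fever cases that 4.10 expects the CHWs to see, 20.5 and 102.4 are about 0.5% and 2.4%.

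**The case against.** **Material not shown may close the gap.** Inclusion refers to community guidelines based on a simplified IMCI algorithm, 4.11 refers to the manufacturer's instructions, 4.7 to the picture chart and 6.1 to a training manual. Any of these could set a lower limit or say what to do. This stands to the extent that one cannot claim a CHW would have to improvise. It does not remove the point: the protocol defines eligibility and prints a dose table, the two do not meet, and no floor or row is stated in either place.

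**The numbers are soft.** This stands. The link between weight and age has no source in the document, 4.10 itself calls its incidence inputs arbitrary, and an average under-five fever rate is applied to young infants. Infants excluded as severely ill or as recently enrolled are not subtracted. The upper end combines the longer age window with the larger of two under-five counts.

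**The 35 kg gap is trivial.** Largely true. It looks like a slip in the inequality sign of the last row and would affect few patients.

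**Two stronger readings are not supported.**

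- A reader might infer that the primary outcome is undermined because such infants sit in the denominator without a defined prescription. The outcome in 4.9 is the proportion prescribed Coartem out of all included patients. It is binary and defined for everyone: an infant not given the drug counts as not prescribed. Each CHW also alternates weekly, so such infants would be expected under both conditions.
- A reader might infer that the picture chart and the weight table conflict. Nothing in the protocol shows them giving different doses, and a chart can be used to choose among packs made up by weight. The chart needs to be brought into the reconciliation, but no contradiction between the two is shown.

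**Conclusion.** The point holds as a patient-safety inconsistency between eligibility and dosing: patients under 5 kg are eligible, and the protocol states no dose for them. Whether unseen guidance fills the gap cannot be judged from the document. The single unassigned weight of 35 kg is a minor addition.

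The mismatch rests on the printed text alone. Its frequency does not. The range of about 20-100 presentations, with about 8-80 needing a dose, depends on the assumed 1-3 months of life below 5 kg and on the protocol's tentative rates, and should be read as an order of magnitude. No effect on the validity of the primary outcome is claimed. The correction is worth making before enrolment because the gap concerns the youngest patients and is cheap to close.

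**What to change.** Reconcile sections 4.5 and 4.6 with the table in 4.7 so that every eligible weight falls in exactly one row or is named as not eligible. In the same edit:

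- Close the gap at 35 kg, and say whether the rows mean completed kilograms.
- Check the picture chart in 4.7 and the weight-based packs in 4.11 against the corrected table, and state how the chart relates to it.
- If the simplified IMCI guidelines or the manufacturer's instructions already contain a limit, bring it into the protocol text.

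Which limit, dose or referral rule applies is for the sponsor and clinical investigators to decide; none is proposed here. The cost is a few lines of protocol text and one item in CHW training. At the planning level there is no material effect on the sample size.
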